## 6 Trial Flow Chart

[figure not shown]

### Key

^ The 45 day screening period may be extended if patients have an exacerbation that requires steroid or antibiotic use. This period will be extended by at least the equivalent time of steroid use added onto the 45 day period or up to the discretion of the PI where clinical judgement is required.

‡ Patients who have failed screening because of changes to trial inclusion/exclusion criteria or did not attend screening due to medical reasons (i.e. an exacerbation) and their medical status has now changed may be rescreened if they are keen to participate in the trial and happy to undergo a repeat screening, at the discretion of the PI and based on clinical judgement

‡ Patients who have attended the imaging visit but do not progress within 14 days onto the trial due to the necessity to investigate abnormalities on the PET-CT / MRI scan may be considered for subsequent entry onto the trial without undergoing a repeated imaging visit, if performed within a reasonable timeframe, and at the discretion of the PI and based on clinical judgement.

\* Fixed between the dates specified (unless file noted for a specific reason) \*\* ± 96 Hours or as indicated

All the above mentioned procedures as per key can take place ± 96h or as indicated. V8, the FDG-PET/CT and MRI imaging visit can occur at any time between Days 105-111. V9 can occur any time from Day 109-112. However, if there is a specific reason why this may not occur, the deviation will be logged in the Trial File. In some cases, the FDG-PET/CT and MRI scans (Imaging Visits 2 and 8) will occur on the same day but it is very likely that scans be done on separate visits during the intervals indicated above. In the event LFT abnormalities are seen, LFT monitoring may need to occur more frequently, as determined by the investigator and medical monitor.

## **7 Introduction**

### **7.1 Background**

Chronic obstructive pulmonary disease (COPD) is the fourth leading cause of death globally and the only major cause that is predicted to increase in the coming decades. Although COPD is initially a pulmonary disease (traditionally caused by cigarette smoke, but increasingly by biomass fuel exposure), it is a complex condition in which outcome is in large part, driven by cardiovascular and systemic components. Consistent with this, although current bronchodilator-based interventions have demonstrated reduced exacerbation rates, this has only addressed part of the burden of disease. In particular, drugs currently used neither reduce the rate of disease progression nor mortality, creating a space in the market for products which could do so. This unmet need and the implied requirement for new strategies for the development of non-bronchodilator therapies for COPD have been recognized by Regulatory agencies as evident from recent guidance documents from the EMA and FDA.

The role of inflammation in COPD is well-recognised. A range of inflammatory markers and cytokines are raised in COPD patients, and relate to the severity of lung function and important clinical outcomes such as admission, cardiovascular events and death. Elevated fibrinogen (indicating a systemic 'inflammatory' phenotype) is a robust, stable biomarker that occurs in at least 25% of patients with COPD, and is associated with increased morbidity and mortality. Inflammation modulates large artery stiffness, an independent determinant of cardiovascular mortality, and anti-inflammatory therapies reduce arterial stiffness, providing a novel mechanism by which inflammation may drive cardiovascular risk.

Losmapimod is a ATP binding site inhibitor of p38 $\alpha$  MAPK and is currently being developed by GSK for a variety of inflammatory conditions, including COPD.

The ERICA programme is a series of studies designed to clarify the role of inflammation in extra-pulmonary disease manifestations in COPD. This trial will assess the role of stratifying patients on the basis of systemic inflammatory biomarkers against parameters of vascular, pulmonary and skeletal muscle phenotypes. This may enable the development of better biomarkers to design smaller, more efficient phase I-III clinical trials of novel drugs that target inflammatory COPD subsets thereby reducing attrition of new medicines.

## **8 Rationale for Trial**

Data from a GlaxoSmithKline (GSK) sponsored observational cohort trial, ECLIPSE, confirmed that cardiovascular disease is common in COPD. Pooled data from large clinical trials of drugs currently in use suggest an equivalent probability of participants dying from cardiovascular or respiratory causes. Moreover, large cohort studies suggest that drugs active against cardiovascular manifestations (for example statins or ACE inhibitors) both reduce mortality and admission with acute exacerbation of COPD. The precise underlying mechanisms by which this may occur have not been completely elucidated, and these may be exaggerated in certain COPD sub-types.

The cardiovascular manifestations in COPD may vary in their pathophysiological origins. Reduced nitric oxide bioavailability (endothelial dysfunction), aortic stiffening and direct vascular inflammation are all potential candidates, as is accelerated atheroma formation. Elevated fibrinogen (indicating a systemic 'inflammatory' phenotype) is a robust, stable biomarker that occurs in at least 25% of patients. It is associated with increased mortality

and morbidity (unpublished data from ECLIPSE). Indeed, this subset has an almost three-fold elevated risk of cardiovascular admissions suggesting that systemic inflammation may accelerate cardiovascular disease.

Atherosclerosis is characterized by the accumulation of lipids, inflammatory cells and connective tissue cells within the arterial wall. It is a chronic progressive disease with a long asymptomatic phase. Over the past decade, the accumulated evidence indicates that inflammation plays a central role in the pathophysiology of atherosclerosis. Indeed, the p38 MAPK cascade appears to play a key role in the initiation and progression of inflammatory diseases. It is therefore likely that inhibition of this enzyme, and its ensuing signal transduction pathway, could attenuate the initiation and maintenance of atherosclerotic events, suggesting a possible therapeutic potential for a p38 MAPK inhibitor in modulating vascular inflammation associated with COPD.

Rupture of atherosclerotic plaques can lead to myocardial infarctions and cause sudden cardiac deaths. Such vulnerable plaques have typical histopathological features that include the presence of a thin fibrous cap, extensive lipid core and an associated inflammatory infiltrate. Macrophages, key inflammatory cells, abound in these plaques and imaging of these macrophages is an appealing approach to detect plaque inflammation that may lead to clinical complications. Recently, FDG-PET/CT has demonstrated success in detecting plaque inflammation within the aorta, carotid and vertebral arteries and has been validated histologically, as correlating with macrophage content and/or activity, both in human and animal models of disease. COPD patients have previously been demonstrated to have increased FDG uptake suggesting increased background vascular inflammation in this group.

The main goals of this experimental trial are to test the hypothesis that stratifying a COPD population on plasma fibrinogen improves the ability to observe response to an anti-inflammatory treatment known to reduce fibrinogen as well as reduce inflammatory activity in the extra-pulmonary and pulmonary spaces in these patients. Therefore, Losmapimod will be used as a tool to test the hypothesis that it improves vascular health in inflamed COPD patients.

FDG-PET/CT imaging will be used to assess Losmapimod's effects on inflammatory activity within aortic and carotid vessels, as well as pulmonary and other extra-pulmonary spaces in an enriched population of COPD patients, characterised by high plasma fibrinogen at baseline. A panel of biomarkers, including endothelial function will also be measured. The American Heart Association's conventional classifications of plaques have been amended to allow MRI classification of plaque. In addition, T2 mapping is a relatively new technique that has been developed to detect and quantify oedema and hydration status of the aortic wall. We aim to assess the effect of p38 inhibition on plaque and aortic wall characteristics in an MRI (T1 and T2 weighted) sub-trial of the carotids and aorta. Endothelial function will be assessed using flow mediated dilatation. Arterial stiffness (as measured by aortic pulse wave velocity) has been shown to be a powerful predictor of cardiovascular mortality. Therefore this trial will provide an opportunity to measure aortic pulse wave velocity to determine the extent to which a p38 MAP kinase inhibitor can mediate changes after a 16 week treatment period in COPD patients.

Inflammation mediates various stages of atherosclerosis development and progression from initial leukocyte recruitment to eventual rupture of the high risk plaque. F-deoxyglucose (FDG) is a synthetic tracer that mimics the biochemical behavior of the natural glucose molecule. FDG positron emission tomography (FDG-PET) has been established to be useful for detecting not only tumor cells, but also inflammatory cells that are metabolically active.

Arterial FDG uptake was first noted in patients undergoing PET for cancer staging. After balloon aortic injury in a rabbit model of atherosclerosis, FDG uptake in atherosclerotic regions correlated strongly with macrophage content ( $r=0.93$ ,  $p<0.002$ ) findings confirmed by others. In the first prospective trial in man, levels of inflammation measured as accumulation rate of FDG were 27% greater in the culprit carotid after recent stroke or TIA than in the contra lateral vessel though with contemporary therapy this difference is not apparent beyond 38 days of the event. Autoradiography of carotid plaque specimens reported in the same paper confirmed co-localisation of tracer to regions of macrophage staining. Further work has confirmed FDG uptake correlates with areas of macrophage (CD68+) staining ( $r=0.96$ ,  $p<0.001$ ), and is independent of plaque thickness, area or luminal stenosis. FDG uptake is thought to reflect activation status of macrophages though recent work by Folco suggests that hypoxia known to exist within atherosclerotic plaque may also be an important determinant of glucose (and hence FDG) uptake into these cells. Nevertheless, FDG-PET remains the best validated tracer in molecular atherosclerosis imaging.

FDG accumulation within the arterial wall could be used to quantify the therapeutic effectiveness of Losmapimod. As a functional imaging modality, FDG positron emission tomography (PET) alone may have some limitations in quantifying the extent of atherosclerosis, as it does not give any information about the morphology of the arterial wall, such as thickness or volume and location and structural details of plaque(s). Therefore a combined PET/CT scanner will be used for this project. Combined PET/CT scanners have several advantages over standalone machines. Firstly, they allow accurate (within 1mm) co-registration of the PET images, with no need for further co-registration software. Secondly, accurate attenuation correction of the PET dataset is possible using the CT images. This shortens the scan time for the patient compared to stand alone PET and CT scanners.

Thirdly, the use of PET/CT combined scanners has been evaluated in a similar patient group and has been found to be a reliable and reproducible technique. In addition, due to limits on radiation exposure in research Participants, PET-CT will not allow for the accurate characterisation and delineation of plaque from vessel wall. As MRI works on the principle of differentiating water and fat resonance, it is the best imaging modality for identifying anatomical plaques without increasing radiation. Scans will be performed on GE scanners in Cambridge (or Siemens in London), thereby allowing co-registration of PET-CT with MRI.

## **9 Trial Design**

### **9.1 Statement of design**

This is a randomised, repeat-dose, double-blind, placebo-controlled, parallel-group trial.

### **9.2 Number of Sites**

There will be 2 sites taking part namely Cambridge University Hospitals NHS Foundation Trust and Royal Brompton & Harefield Foundation NHS Trust. The co-ordination of the clinical trial will be performed by the Cambridge Clinical Trials Unit, Cambridge University Hospitals NHS Foundation Trust. The imaging centre the Royal Brompton & Harefield NHS Foundation Trust is performed by Imanova clinical Imaging Centre, Burlington Danes building Imperial College London, Hammersmith Hospital.

### **9.3 Number of Participants**

A sufficient number of patients with COPD will be enrolled across the 2 participating sites, so that approximately 60 participants with data suitable for the primary statistical analysis (approximately 30 per arm) complete the trial.

### **9.4 Trial duration**

The expected duration of the trial is up to 2.5 years. Participants will be enrolled into the trial over a period of approximately 24 weeks. A full break down of screening through to follow-up can be found in Section 6 page 15 -Trial Flow Chart.

### **9.5 Trial objectives**

#### **9.5.1 Primary Objectives**

To determine the effect of Losmapimod in COPD patients on vascular structure and function as assessed by:

1. Vascular inflammation
2. Endothelial function
3. Arterial structure and plaque characteristics (optional sub-study)

#### **9.5.2 Secondary Objectives**

To determine the effects of Losmapimod on:

1. Inflammation in lung tissue
2. Inflammation in fat
3. Arterial stiffness
4. Blood biomarkers of inflammation
5. Indices of lung function and physical performance
6. Body composition and fat
7. Safety and tolerability

### **9.6 Trial endpoints**

#### **9.6.1 Primary endpoints**

Change in vascular inflammation (using derivatives of Standard Uptake Value (SUV) and Tissue to Background Ratio (TBR) in the carotid and aortic arteries of patients following 16 weeks of treatment.

Change in flow mediated dilatation post-ischaemia and/or flow mediated dilatation post-Glyceryl trinitrate, following 16 weeks treatment.

Change in atheromatous plaque and vessel wall characterisation using MRI and/or FDG-PET/CT, following 16 weeks of treatment. MRI analysis will be dependent on a sufficient number of datasets since this was an optional sub-study (please see section 15 of the protocol for further details).

#### **9.6.2 Secondary endpoints**

Change in lung inflammation assessed by FDG-PET/CT, following 16 weeks of treatment.

Change in visceral and subcutaneous fat inflammation and serum/plasma measures of systemic inflammation, following 16 weeks of treatment.

Change in arterial stiffness measures (aortic pulse wave velocity and augmentation index), following 16 weeks of treatment.

Change in baseline corrected blood concentration of biomarkers.

Change in spirometry (FEV1, FVC, FEV1/FVC ratio), maximal sniff nasal inspiratory pressures and 6 MWT following 16 weeks of treatment.

Change in body composition as measured by BMI and FFMI, following 16 weeks of treatment.

Safety and tolerability parameters, including physical examination, blood pressure, heart rate, 12-lead electrocardiogram (ECGs) recordings, clinical laboratory tests, lung function, and adverse event reporting.

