| Trial Endpoints               | 
Primary:
 
Change in vascular inflammation (using derivatives of Standard Uptake Value (SUV) and Tissue to Background Ratio (TBR)) in the carotid and aortic arteries of participants following 16 weeks of treatment.
 
Change in flow mediated dilatation post-ischaemia and/or flow mediated dilatation post-glyceryl trinitrate, following 16 weeks of treatment.
 
Change in atheromatous plaque and vessel wall characterisation using MRI and/or FDG-PET/CT, following 16 weeks of treatment (MRI is an optional sub-study and analysis will be based on a sufficient number of datasets).
 
Secondary:
 
Change in lung inflammation assessed by FDG-PET/CT, following 16 weeks of treatment.
 
Change in visceral and subcutaneous fat inflammation and serum/plasma measures of systemic inflammation, following 16 weeks of treatment.
 
Change in arterial stiffness measures (aortic pulse wave velocity and augmentation index), following 16 weeks of treatment.
 
Change in baseline-corrected blood concentration of biomarkers.
 
Change in spirometry (FEV1, FVC, FEV1/FVC ratio) and maximal SNIP and 6MWT following 16 weeks of treatment.
 
Change in body composition as measured by BMI and FFMI, following a 16 week treatment.
 
Safety and tolerability parameters, including physical examination, blood pressure, heart rate, 12-lead electrocardiogram (ECGs) recordings, clinical laboratory tests, lung function, and adverse event reporting.
 |

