#### **12.1.1 Timing of assessments**

Please refer to Table 7 page 55 for timings of assessments

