### **12.1.2 Screening, V1 (Day -45 to Day -14)**

Participants will attend the unit for a screening visit within 45 days prior to administration of the first dose of trial medication (V3). Written informed consent must be obtained prior to performance of any protocol specific procedures. The following procedures will be performed:

- Medical history including smoking history.
- Current medication history prior to the screening visit.
- Demography (date of birth, age, gender and race).
- Physical examination including height, weight, BMI, vital signs.
- 12-lead ECG (triplicate).
- Spirometry post bronchodilator.
- Following an overnight fast, blood (approximately 55ml) and urine will be collected for clinical chemistry (including urea, creatinine, uric acid, electrolytes, liver function and glucose and HbA1c if diabetic), Full Blood Count (including haemoglobin, platelets and differential white cell count), HIV, Hepatitis B surface antigen, Hepatitis C antibody, urinalysis.
- Biomarkers.

Participants detailed cardiovascular and respiratory (and other systems) medical history will be collected, including information regarding any known allergies to drugs, use of concomitant medications, detailed history of smoking and alcohol consumption and history of blood donation and/or participation in clinical trials. The 45 day screening period may be extended if patients have an exacerbation that requires steroid or antibiotic use. This period will be extended by at least the equivalent time of steroid use added onto the 45 day period or up to the discretion of the PI where clinical judgement is required. Patients who have failed screening because of changes to trial inclusion/exclusion criteria or did not attend screening due to medical reasons (i.e. an exacerbation) and their medical status has now changed may be rescreened if they are keen to participate in the trial and happy to undergo a repeat screening, at the discretion of the PI and based on clinical judgement.

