### **12.1.6 V10 Follow-up (Days 120 -126)**

Participants will return to the unit within approximately 1-2 weeks after the last scan, and will undergo the following procedures:

- Physical examination including seated blood pressure (BP) and heart rate (HR).
- Blood (approximately 55mL) and urine will be collected for clinical chemistry, haematology, urinalysis.
- Bloods for biomarkers.
- Adverse event and concomitant medication check.

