## **12.9 Safety**

Clinical safety data is a secondary endpoint of this Phase 2 trial. The safety and tolerability of protocol-specified treatments will be assessed by physical exam findings, 12-lead ECGs recordings, vital sign (blood pressure and heart rate) measurements, clinical laboratory tests, clinical monitoring /observation and spontaneous and elicited adverse event reporting.

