### **Secondary:**

Change in lung inflammation assessed by FDG-PET/CT, following 16 weeks of treatment.

Change in visceral and subcutaneous fat inflammation, and serum/plasma measures of systemic inflammation, following 16 weeks of treatment.

Change in arterial stiffness measures (aortic pulse wave velocity and augmentation index), following 16 weeks of treatment.

Change in baseline corrected blood concentration of biomarkers.

Change in spirometry (FEV1, FVC, FEV1/FVC ratio), sniff nasal inspiratory pressures and 6MWT following 16 weeks of treatment.

Change in body composition as measured by body mass index (BMI) and free fat mass index (FFMI), following a 16 week treatment.

Safety and tolerability parameters, including physical examination, blood pressure, heart rate, 12-lead electrocardiogram (ECGs) recordings, clinical laboratory tests, lung function, and adverse event reporting

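### Change in BMI and FFMI at 16 weeks is a secondary endpoint, but the readable protocol lists no week-16 weight and gives FFMI neither a visit nor a method

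*Protocol*

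**What the plan says.** Secondary objective 6 in protocol section 9.5.2 is "Body composition and fat". Its endpoint is stated three times with the same two measures and the same time point:

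- Section 9.6.2: "Change in body composition as measured by BMI and FFMI, following 16 weeks of treatment"
- Section 15, Secondary: "Change in body composition as measured by body mass index (BMI) and free fat mass index (FFMI), following a 16 week treatment"
- Section 5, Trial Synopsis: "Change in body composition as measured by BMI and FFMI, following a 16 week treatment"

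On collection, section 12.1.2 lists at V1: "Physical examination including height, weight, BMI, vital signs". Section 12.1.1 sends the reader to the Time and Events Table: "Please refer to Table 7 page 55 for timings of assessments". Section 12.9 describes vital signs in these words: "vital sign (blood pressure and heart rate) measurements". The follow-up examination at V10 (section 12.1.6) names seated blood pressure and heart rate and nothing else. Sections 12.5 and 12.6 give methods for flow mediated dilatation, SNIP, arterial haemodynamics and the walk test, but none for body composition.

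**The concern.** A change endpoint needs a value before treatment and a value at the stated time, both obtained by a known method. Here the endpoint fixes two measures and a time point, but the part of the protocol that tells sites what to do at each visit does not ask for the measurements. A site that followed the readable lists exactly would reach the end of treatment with a screening BMI and nothing to compare it with, and with no FFMI at all.

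This is a question of data collection, so a statistical analysis plan cannot repair it. A weight or fat-free mass that was not measured at week 16 cannot be obtained later. At stake is one of seven secondary objectives. If sites weigh participants unprompted, the days, the equipment and the completeness will vary between the two centres.

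**Working it through.** The protocol states no figure on this point that could be reproduced. The check is a comparison of the endpoint with the schedule.

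**What is needed.** 2 measures (BMI, FFMI) x 2 time points (before treatment, week 16) = 4 values per participant.

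**What the readable text lists at each visit.**

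| Visit | Days | Weight or BMI listed? | FFMI listed? | Source |
|---|---|---|---|---|
| V1 | -45 to -14 | Yes, in the physical examination | No | 12.1.2; synopsis, screening procedures |
| V2 | -14 to -1 | No | No | 12.1.3, 12.1.4 |
| V3 | 1 | No; vital signs only | No | 12.1.5 |
| V4 to V7 | 14, 28, 56, 84 | No; vital signs only | No | 12.1.5 |
| V8 | 105-111 | No; scans and adverse events | No | 12.1.5 |
| V9 | 109-112 | No; vital signs only | No | 12.1.5 |
| V10 | 120-126 | Not named; examination cites blood pressure and heart rate | No | 12.1.6 |

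**Could vital signs include a weight?** Section 12.9 describes them as blood pressure and heart rate. The V1 list names weight and BMI alongside vital signs, as separate items. So the vital signs at V3 and V9 do not supply a weight.

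**Could V10 serve?** Table 7 has one physical examination row, ticked at V1 and V10, so a weight at V10 is possible. The synopsis, however, names height, weight and BMI for the V1 examination and leaves them out for V10. The timing is also wrong. The last treatment day is Day 112, and 112/7 = 16.0 weeks. V10 falls 120 - 112 = 8 to 126 - 112 = 14 days later, at 120/7 = 17.1 to 126/7 = 18.0 weeks, off treatment.

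**Is there an FFMI method?** The term appears in the abbreviation list and in the three endpoint statements. It has no procedure section and no Table 7 row. Section 12.5.2, on muscle assessment, covers SNIP only.

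**Count of explicitly listed values.** BMI before treatment 1, BMI at week 16 0, FFMI before treatment 0, FFMI at week 16 0. Total 1 of 4, so 4 - 1 = 3 are not listed.

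**Comparison with other endpoints.** Arterial haemodynamics, flow mediated dilatation, SNIP, spirometry and the walk test are each listed at V3 and V9, both in section 12.1.5 and in Table 7. Body composition is missing from the V3 and V9 entries in both places, so a table damaged in conversion is an unlikely explanation.

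**The case against.** The strongest reply is that the schedule has not been seen in full. Section 9.4 calls the Section 6 flow chart the full breakdown from screening to follow-up, and only its key is readable. Nothing can be said about what the figure contains. This stands, and it limits the point to the readable text.

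Second, absence from Table 7 proves little alone. Section 12.1.5 lists an adverse event assessment at V8 and tablet counts at V4 to V7. The table has no tick for the first and no row for the second. This also stands, which is why the visit lists carry the argument and the table only supports it.

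Third, a reader might infer that neither change can be computed for any of the approximately 60 participants. The documents do not support that for BMI. The main imaging measures derive from SUV. If SUV is normalised to body weight (an assumption, since section 16.1 does not state the normalisation), weights would exist at V2 and V8, and with the V1 height they would give a change in BMI. Section 12.1 also says that further procedural detail is in the Trial Procedures Manual and the eCRFs, which may call for a weight. Neither source is stated in the protocol, and a PET-visit weight would not yield FFMI.

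Fourth, a reader might infer that the endpoint list and the schedule contradict each other. They do not: nothing in the text says that body composition will not be measured. This is an omission.

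Finally, the consequence is modest. The trial is described as exploratory, and secondary endpoints receive summary measures, with regression analysis optional.

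**Conclusion.** The point holds for the readable protocol. FFMI change has no scheduled data, either before treatment or at week 16, and no method. BMI change has a screening value but no scheduled week-16 value, unless a weight is taken at the PET visits or under the Trial Procedures Manual. One of the four values needed per participant is explicitly listed.

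The conclusion is firm for FFMI and weaker for BMI. It assumes that the unseen Section 6 flow chart adds no weight or body-composition measurement, and that V10, being off treatment, does not count as the 16-week value. If the Trial Procedures Manual or the eCRF already specifies these measurements, what remains is a missing cross-reference in the protocol. The primary endpoints are unaffected. The gap should be corrected because the data cannot be recovered afterwards and most of the remedy is nearly free.

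**What to change.** 1. Add body weight to the V3 and V9 lists in section 12.1.5, with BMI calculated from the V1 height, and add a matching row to Table 7 ticked at both visits.
2. Keep FFMI only if a named method is already available at both sites. In that case, describe it in section 12.5 and schedule it at V3 and V9. Otherwise delete FFMI from the synopsis, section 9.6.2 and section 15, and keep BMI alone.
3. State in the amendment from which participant onwards the endpoint can be analysed.

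The cost is about a minute of weighing at two visits that participants already attend. If FFMI is deleted, the trial loses it as an endpoint. Buying a device to rescue FFMI would be an added procedure and is not recommended on this ground alone. Participants already past V9 cannot be recovered, unless a suitable weight was recorded for another purpose, and that would help BMI only.
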